**Sample Size Determination:** We have identified a convenience sample of 318 participants as feasible based on our methods of recruitment and study timelines. Based on our current study of a 'virtual cardiac rehabilitation program' in Northern BC which has a reported drop-out rate of 12%, we have set a drop-out rate of 15% due to patient withdrawal, death and moving outside of the province, and will therefore finish with 270 participants. We will collect detailed information on the subjects who withdraw and their reasons for withdrawing. In our pilot combined clinic at St. Paul's Hospital for patients with two or more of cardiovascular disease, diabetes and chronic kidney disease, we observed 32 hospitalizations over a two-year period in the 30 usual care patients (a baseline event rate of 107%) compared to 24 hospitalizations over a two-year period in 34 patients in the combined pilot clinic (event rate of 71%) resulting in a 33.6% reduction in events. We have based the current study power estimates on a 25% reduction in hospital admissions by the iCDM. We have chosen a more conservative effect of the iCDM as the iCDM is directed more at supporting patient self-management and monitoring, and does not involve direct medical management. Based on a 25% reduction in hospital admissions, and an alpha of 0.05, we have outlined the power given the following estimated event rates using the method of Demidenko E in the table below. We have provided a range of event rates as we do not have documented event rates from our targeted patient population. If the event rate is similar to that observed in our pilot clinic at St. Paul's Hospital, we will have sufficient baseline events for a power greater than 0.80 to detect an effect of 25% reduction in events.

| Usual Care* | iCDM* | Power |
|--------------------|--------------|--------------|
| 40%                | 30%          | 0.39         |
| 50%                | 38%          | 0.55         |
| 60%                | 45%          | 0.67         |
| 70%                | 53%          | 0.78         |

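### In the power table, the 70% row prints 0.78 where the stated inputs give about 0.83; the error is conservative and the other rows reproduce or nearly so

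*Protocol*

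**What the plan says.** All of this stands in the protocol's Sample Size Determination paragraph. The trial enrols a "convenience sample of 318 participants", allows 15% drop-out, and "will therefore finish with 270 participants". On the effect size it says "We have based the current study power estimates on a 25% reduction in hospital admissions by the iCDM". The power statement opens "Based on a 25% reduction in hospital admissions, and an alpha of 0.05", and the values were obtained "using the method of Demidenko E"; the two references cited there (56 and 57) are, by their titles, on sample size for logistic regression.

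The table, introduced with "we have outlined the power given the following estimated event rates", gives:

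| Usual care | iCDM | Power |
|---|---|---|
| 40% | 30% | 0.39 |
| 50% | 38% | 0.55 |
| 60% | 45% | 0.67 |
| 70% | 53% | 0.78 |

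The paragraph does not say whether the table uses 270 or 318, whether the test is two-sided, or which odds ratios were entered. Both rate headings carry an asterisk whose footnote is not in the text available.

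**The concern.** The table is the paragraph's row-by-row account of what the trial can detect, and the authors say that they have no documented event rates for their target population. A reader therefore uses it to judge how high the event rate must be for adequate power. As printed, even a 70% usual-care rate falls short of 0.80. If the 70% figure does not follow from the inputs given beside it, the reader places that threshold too high and cannot tell which effect size the figure belongs to.

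**Working it through.** **Inputs.** From Sample Size Determination: N = 270 (318 × 0.85 = 270.3), alpha 0.05, relative reduction 25%, logistic-regression method. Assumed: two-sided test; 1:1 allocation, so 135 per arm (the block sizes of 2, 4 and 6 under Randomization are consistent with this); and a yes/no outcome, as a logistic method for two proportions implies.

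**Formula.** Wald test of the log odds ratio, with p0 the usual-care rate and p1 = 0.75 × p0:

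Power = Φ( |ln OR| / SE − 1.96 ), where SE = √[ 1/(135·p0·(1−p0)) + 1/(135·p1·(1−p1)) ].

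**The 70% row.** p0 = 0.70 and p1 = 0.525, so OR = (0.525/0.475)/(0.70/0.30) = 0.474 and |ln OR| = 0.747.
SE = √[ 1/(135 × 0.21) + 1/(135 × 0.2494) ] = 0.255.
0.747/0.255 = 2.93, and Φ(2.93 − 1.96) = 0.834. The printed figure is 0.78.

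**All rows at N = 270, exact 25% reduction.**

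| Usual care | iCDM (exact) | OR | Recomputed | Printed | Recomputed − printed (points) |
|---|---|---|---|---|---|
| 40% | 30% | 0.643 | 0.404 | 0.39 | +1.4 |
| 50% | 37.5% | 0.600 | 0.542 | 0.55 | −0.8 |
| 60% | 45% | 0.545 | 0.691 | 0.67 | +2.1 |
| 70% | 52.5% | 0.474 | 0.834 | 0.78 | +5.4 |

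**Can display rounding explain the 70% row?** No. At the printed 53%, power is 0.814. At 53.5%, the upper limit of what rounds to 53%, it is still 0.792.

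**Can another N or test explain it?**
- N = 318 moves further away: 0.462, 0.610, 0.761 and 0.889.
- The pooled two-proportion formula at 270 gives 0.406, 0.544, 0.696 and 0.843.
- Solving each row for the total N that gives its printed power, at an exact 25% reduction, yields about 258, 276, 257 and 235. The best single N, 255, still misses by 3.3 points in one row.
- The best one-sided fit needs N of about 186, which is not a protocol figure, and misses by 2.3 points.

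**What does reproduce the table.** Odds ratios rounded to the nearest 0.05, at N = 270:

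| Usual care | Rounded OR | Implied iCDM rate | Implied reduction | Power | Printed |
|---|---|---|---|---|---|
| 40% | 0.65 | 30.2% | 24.4% | 0.389 | 0.39 |
| 50% | 0.60 | 37.5% | 25.0% | 0.542 | 0.55 |
| 60% | 0.55 | 45.2% | 24.7% | 0.679 | 0.67 |
| 70% | 0.50 | 53.8% | 23.1% | 0.776 | 0.78 |

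Every row is then within 0.01 of print. Rounding costs little in the first three rows. In the last it takes the odds ratio from 0.474 to 0.50, and so the reduction from 25% to 23.1%.

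**Where 0.80 is reached.** Solving the formula with p1 = 0.75 × p0 at N = 270 gives a usual-care rate of about 67.5%.

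**The case against.** The strongest reply is that the table is sound apart from coarse input. All four figures fit the protocol's own 270 within 0.01 once the odds ratios are rounded, so the sample size is not in doubt and only the effect entered is. The one row clearly off errs on the cautious side. The sample size was fixed by feasibility, so no design decision rests on this row, and neither does the text's claim of power above 0.80 at the pilot clinic's event rate. Much also depends on what the protocol leaves unsaid: N, sidedness and method options.

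Most of this stands and limits the point. A reader might infer from the row-by-row N values that the table mixes sample sizes. The documents do not support that, because one N fits once the effect is allowed to differ slightly from 25%. A reader might also call the 50% row 4 points too high, since the printed 38% gives 0.508 against 0.55. But 38% is the whole-percent display of 37.5%, at which power is 0.542, so that gap comes from the display.

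What the reply does not remove is the 70% row. No iCDM rate that rounds to the printed 53% gives 0.78 at 270, and 318 is further off. If the rounded odds ratio was used, the row's power belongs to 53.8%, which is neither the printed rate nor the stated 25% reduction.

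**Conclusion.** The 70% row is wrong for its stated inputs: about 0.83 (0.81 at the printed 53%) against 0.78. The 60% row is marginally low, 0.69 against 0.67. The 40% and 50% rows reproduce within about 1.5 points. This rests on 270 analysed, 1:1 allocation, a two-sided 0.05 test and a yes/no outcome. Rounded odds ratios are the likely cause, but that is an inference and nothing in the protocol confirms it.

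Two stronger readings should be resisted. The power column as a whole is not wrong. Nor does the table make the trial look better powered than its inputs allow: in the one row clearly off, it does the reverse. The practical effect is that the 0.80 threshold sits at a usual-care rate of about 67.5%, where the table suggests somewhere above 70%.

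The recomputed values hold only if each rate is the proportion of participants with an event. The same paragraph also uses event rate for admissions per patient (32 admissions in 30 pilot patients, given as 107%), and the asterisk footnote that may define the table's rates is not in the text available. The meaning is for the sponsor to state. This is a minor correction.

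**What to change.** Recompute the power column from the unrounded 25% reduction at the N that the table is meant to use; at 270, under the assumptions above, it reads 0.40, 0.54, 0.69 and 0.83. Print the iCDM rates as 37.5% and 52.5%. Add a line giving the N, the sidedness, the allocation and the odds ratios entered. State what the event rates mean, or confirm that the asterisk footnote already does so; if they are not proportions of participants, the column needs a method that suits that outcome. The cost is one corrected table and a sentence or two, with no change to recruitment, conduct or analysis.

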## STATISTICAL ANALYSES

We anticipate that 10% of the study population will be lost-to-follow-up at the end of study. Lost-to-follow-up will be defined as those participants who have died, withdrawn from the study or moved out of the province. Every effort will be made to obtain final data on the primary and secondary outcomes from subjects regardless of the extent of study participation to that point. *Lack of compliance to the iCDM will not be a reason for withdrawal from the study.* We will explore differences in baseline variables between those lost-to-follow-up and those who remain in the study.

The primary outcome of hospital admissions between the two groups from baseline to two (dependent variable) years will be modeled using ordered logistic regression with group assignment, age and sex as *a priori* covariates. In the event of potentially clinically relevant differences in baseline factors, we will include these covariates in the model (such as socio-demographics, e-health literacy, depression, and other morbidities). Non-normally distributed continuous variables will be transformed prior to analyses. Residual plots for the primary outcome models will be plotted and assessed for model adequacy. Secondary outcomes between the two groups will be compared using the Pearson Chi-square test for categorical variables and independent samples t-test for continuous variables. All analyses will be governed by intent-to-treat with no group crossovers.

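### The stated power above 0.80 at the pilot admission rate is wrong: a mean count of 1.07 admissions per patient is read as a proportion, and the planned 270 completers give about 0.6 at best under the likely assumptions.

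*Protocol*

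**What the plan says.** All of this is in the Protocol.

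- **Basis of the number (Sample Size Determination).** "We have identified a convenience sample of 318 participants as feasible", given the recruitment methods and timelines.
- **Attrition (same section).** "we have set a drop-out rate of 15% due to patient withdrawal, death and moving outside of the province, and will therefore finish with 270".
- **Pilot rate (same section).** "we observed 32 hospitalizations over a two-year period in the 30 usual care patients (a baseline event rate of 107"; the last figure is a percentage.
- **Effect and alpha (same section).** A relative reduction of one quarter at the 0.05 level; whether the test is one- or two-sided is not given.
- **Power method (same section).** "we have outlined the power given the following estimated event rates using the method of Demidenko E". The two references cited for the method are papers on sample size for logistic regression. The table gives power of 0.39, 0.55, 0.67 and 0.78 for usual care rates of 40%, 50%, 60% and 70%.
- **Conclusion drawn (same section).** If the rate resembles the pilot's, "we will have sufficient baseline events for a power greater than 0.80 to detect an effect of 25% reduction in events".
- **Primary analysis (Statistical Analyses).** Admissions over two years "will be modeled using ordered logistic regression with group assignment, age and sex as" prespecified covariates.
- **Attrition again (Statistical Analyses).** "We anticipate that 10% of the study population will be lost-to-follow-up at the end of study", for the same three reasons: death, withdrawal and leaving the province.

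**The concern.** The table and the pilot figure are on different scales. A logistic-regression power calculation needs the proportion of patients with an event. The pilot figure counts admissions, including repeat admissions in one patient, and divides by patients. Both are printed as percentages, so 107% looks like one more row below the 70% row (power 0.78), and power above 0.80 seems to follow. It does not: a mean count of 1.07 has no place on a scale of proportions.

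Every printed row is below 0.80, so this sentence is the only place where the protocol says that the trial could be adequately powered. If it is wrong, a reader of a null result may take it as evidence from an adequately powered trial when a true 25% reduction had a substantial chance of being missed.

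**Working it through.** **Inputs.** From the Protocol: 318 randomised, 15% drop-out, 318 × 0.85 = 270.3 completers, so n = 135 per arm; alpha 0.05; 25% reduction; pilot usual care rate 32/30 = 1.067 admissions per patient. Assumed, because not stated: two-sided test, 1:1 allocation, and the dispersion k of the counts (0 is Poisson; 0.5 and 1 are illustrative).

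**Step 1. Reproduce the printed table.** Treat the rates as proportions and use the Wald test of the log odds ratio:

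b = |ln[p1/(1−p1)] − ln[p2/(1−p2)]|, SE = √{1/[n·p1(1−p1)] + 1/[n·p2(1−p2)]}, power = Φ(b/SE − 1.96).

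Example, 60% against 45%: b = 0.606, SE = 0.247, power = Φ(0.50) = 0.69.

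| Usual care | 25% lower | Printed | Binary | Same rates as Poisson means |
|---|---|---|---|---|
| 40% | 30% | 0.39 | 0.40 | 0.28 |
| 50% | 37.5% | 0.55 | 0.54 | 0.34 |
| 60% | 45% | 0.67 | 0.69 | 0.40 |
| 70% | 52.5% | 0.78 | 0.83 | 0.45 |

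With odds ratios rounded to 0.65, 0.60, 0.55 and 0.50, the binary formula gives 0.389, 0.542, 0.679 and 0.776, so all four rows then agree closely. One-sided testing gives 0.53, 0.66, 0.79 and 0.90, which does not fit. The table behaves as a two-sided binary calculation on about 270 patients, not as a count calculation.

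**Step 2. Put the pilot rate into that formula.** At p = 1.067, p(1−p) = 1.067 × (−0.067), which is negative, so the formula is undefined. Binary power above 0.80 does arise at proportions such as 75% (0.90) or 80% (0.95), but the pilot figure is not such a proportion. If counts were Poisson, the proportions with any admission would be 1 − e^(−1.067) = 65.6% and 1 − e^(−0.80) = 55.1%, and binary power would be 0.42.

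**Step 3. Power for counts at the pilot rate.** The means are 1.067 and 0.75 × 1.067 = 0.80, and |ln 0.75| = 0.2877.

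SE = √[(1/1.067 + 1/0.80 + 2k)/135], power = Φ(0.2877/SE − 1.96).

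- k = 0: SE = √(2.1875/135) = 0.1273; power = Φ(0.300) = 0.62.
- k = 0.5: SE = √(3.1875/135) = 0.1537; power = Φ(−0.088) = 0.47.
- k = 1: SE = √(4.1875/135) = 0.1761; power = Φ(−0.327) = 0.37.

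**Step 4. Power for the planned ordinal analysis.** The score test of a proportional-odds model with group alone is the tie-corrected rank test. Simulated with 135 per arm, it gives power of about 0.58 (k = 0), 0.40 (k = 0.5) and 0.31 (k = 1), each good to about 0.01. No gain from the age and sex covariates is included.

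**Step 5. More favourable settings, all with Poisson counts.**

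| Setting | Power |
|---|---|
| 10% loss (318 × 0.90 = 286), rate test | 0.64 |
| All 318 analysed, rate test | 0.69 |
| All 318 analysed, ordinal | about 0.65 |
| 270 completers, one-sided, rate test | 0.73 |
| All 318, one-sided, rate test | 0.79 |

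None reaches 0.80. With 270 completers and a two-sided test, 0.80 on the rate-difference scale would need a variance-to-mean ratio of (0.267² × 135)/(1.867 × 2.80²) ≈ 0.66, that is, counts clearly less variable than Poisson.

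**Step 6. Detectable reduction.** Under the ordinal test with 135 per arm, power of about 0.80 needs a reduction of about 32% (k = 0), 39% (k = 0.5) or 44% (k = 1).

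**The case against.** **The sample size does not depend on the sentence.** A reader might infer that 318 was justified by the power claim alone. The protocol does not support that: it presents 318 as a feasible convenience sample and describes power afterwards. This stands. Removing the sentence leaves the stated basis for 318 intact and creates no call for more patients.

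**The protocol is already candid.** It says that event rates in its target population are not documented, prints four rows that are all below 0.80, and makes the claim conditional on a pilot-like rate. This also stands and limits the risk of misreading. But the conditional statement is still false when its condition is met.

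**0.6 is not a strict ceiling.** It rests on two-sided testing, exactly 270 analysed, no covariate gain, and counts at least as variable as Poisson. The plan also promises every effort to obtain final data on all participants. That is fair, and the figure should be given with its assumptions. Relaxing the first two, singly or together, still leaves power below 0.80 (0.79 at most), and variability below Poisson is unlikely for repeat admissions.

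**Is the table binary?** The 70% row matches closely only with a rounded odds ratio, and the note belonging to the asterisks on the rate columns is not in the text available. The cited method and the other rows point to a binary calculation. Either reading leaves the sentence unsupported: as a proportion, 107% is impossible; as a mean count, power falls short.

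**Smaller detectable effects.** A rate test would suggest that reductions of about 30% (Poisson) or 36–40% (dispersion 0.5 to 1) are detectable with 0.80 power. Those values do not carry over to the planned ordered logistic analysis, where they give only about 0.76, 0.74 and 0.71, so they should not be put into the protocol.

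**Conclusion.** The sentence is wrong as written. At the pilot rate, 270 completers give about 0.62 power for a 25% reduction by a Poisson rate test and about 0.58 by the rank approximation to the planned ordinal analysis. Under assumed dispersion of 0.5 or 1, the ordinal figure is about 0.40 or 0.31. A realistic statement is therefore roughly 0.3 to 0.6, so a true 25% reduction would be missed about 40% to 70% of the time.

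That the claim fails does not depend on the dispersion values, which are assumptions; Poisson counts already fall short. The lower end of the range does depend on them.

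The 15% and 10% attrition figures contradict each other for the same three reasons for loss, and 10% is below the 12% seen in the team's own study. The effect is small, about 2 to 3 points of power, and the power section uses the more cautious value.

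**What to change.** 1. In Sample Size Determination, delete the sentence claiming power above 0.80.
2. Replace the table with power for mean admissions per patient under the planned ordered logistic model, stating the sidedness of alpha and the dispersion assumed (for example 0, 0.5 and 1). Label the pilot figure as 1.07 admissions per patient, not 107%.
3. State that 270 completers give roughly 0.3 to 0.6 power for a 25% reduction at the pilot rate, and that 0.80 power under the planned model needs a reduction of about 32% with Poisson counts, about 39% with dispersion 0.5 and about 44% with dispersion 1.
4. Use one attrition figure in Sample Size Determination and Statistical Analyses.

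The cost is some rewording, a recomputed table and a less favourable stated power. No extra patients are needed, and 318 can stay as a feasibility number.

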
**Inclusion Criteria:** Men and women with two or more of the five targeted chronic diseases; daily Internet access (home, work or other environment) by any means (such as personal computer, personal data assistant or smartphone); over 19 years of age; and able to read, write and understand English without difficulty.

**Exclusion Criteria:** Patients with significant co-morbidities (excluding the five targeted conditions these include HIV, uncontrolled metabolic/endocrine disorders, prior stroke or other conditions affecting cognitive abilities to

provide consent and participate, alcohol/drug addiction) that may interfere with effective management; patients who have scheduled surgical procedures; and patients who are unable to provide informed consent.

Detailed records will be kept of all individuals who are screened for the study to clearly define the population from which our study cohort will be derived and to ensure our reporting will follow the CONSORT guidelines.

**Study Outcomes:** *The primary outcome will be the difference between the iCDM and usual care groups in hospital admissions from the time of randomization to the end of two years.* Data will be collected by participant self-report and confirmed through access to participant medical records in those who sign the study's Medical Records Release Form. We will also collect data from Provincial Databases hosted by the Population Data BC; Medical Services Plan payment information file, PharmaCare file, hospital separations file and Vital Statistics deaths and clinical deaths on secondary outcomes of healthcare utilization such as length of hospital admissions, emergency room visits, physician/nurse practitioner visits, diagnostic and lab procedures. In addition, secondary outcomes will include patient quality of life, self-management, patient and provider experience, and mortality (see below).

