**Baseline Assessment:** We will collect the following data variables on all consenting participants: social demographics, medical history, current medications, self-management and quality of life, smoking status, alcohol consumption, e-health literacy, and recent diagnostic and lab tests (<6 months). The baseline (and follow-up) assessment will be conducted without the need for the research coordinator to meet with the patient. Data on patient demographics, medical history, current medications, smoking status, and recent diagnostic and lab tests will be abstracted from the patient's physician's/nurse practitioner's medical record and confirmed by telephone with the patient. For all other outcomes we will be using self-administered questionnaires which will be mailed to the patient with a stamped return envelope to mail back. If after two weeks the questionnaires have not been received, the research coordinator will contact the patient by telephone to follow-up. We will create a toll-free number for participants to call the research coordinator to return any messages from the coordinator and ask questions regarding assessment data collection so that participants will not have to incur long-distance phone charges.

**Randomization:** Participants will be stratified by sex and site of recruitment (based on health authority), and then randomized to either usual care or the iCDM using computer-generated variable blocks of 2, 4 and 6 within a web-based randomization system. A research assistant not involved in data collection will access the randomization system using a unique authorization code. The date and time, patient identifiers and randomization codes will automatically be maintained in a transaction file. This same research assistant will be responsible for communicating group assignments to the study participants. Participants will be informed not to discuss their group assignment with the research coordinator responsible for data collection to ensure the study

remains single-blinded. If at the time of being informed of their group assignment, the participant becomes distressed, anxious or upset, the research coordinator will inform the participant that the study psychologist is available to discuss their concerns if they wish.

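### Admissions before randomisation are not specified as a baseline variable, a data look-back or a covariate, although admissions are the primary outcome

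*Protocol*

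**What the plan says.** - **Outcome.** Study Outcomes defines the primary outcome as the group difference in "hospital admissions from the time of randomization to the end of two years".
- **Baseline data.** Baseline Assessment lists "social demographics, medical history, current medications, self-management and quality of life, smoking status, alcohol consumption, e-health literacy, and recent diagnostic and lab tests". Medical history and several other items "will be abstracted from the patient's physician's/nurse practitioner's medical record and confirmed by telephone with the patient". Laboratory tests carry a six-month look-back; medical history carries neither a definition nor a look-back. Additional Variables Assessed at Baseline adds a depression scale and specifies the e-health literacy scale.
- **Database request.** Study Outcomes names the "Medical Services Plan payment information file, PharmaCare file, hospital separations file and Vital Statistics deaths", to be used "on secondary outcomes of healthcare utilization such as length of hospital admissions, emergency room visits" and similar items. Neither that paragraph nor Healthcare Utilization gives a start date for the extraction.
- **Follow-up.** Participants are asked about admissions at one year and at two years.
- **Randomisation.** Strata are sex and health authority.
- **Analysis.** Statistical Analyses says the primary outcome will be "modeled using ordered logistic regression with group assignment, age and sex as" a priori covariates. Other baseline factors enter only if clinically relevant differences appear; the examples given are socio-demographics, e-health literacy, depression and other morbidities.

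**The concern.** Two secondary outcomes, quality of life and self-management, have a specified baseline measurement. The primary outcome has none. For a count of admissions, the obvious prognostic variable is the same count over an earlier period. Eligibility requires two or more of five chronic diseases and sets no condition on past admissions, so stable and frequently admitted patients can both enter.

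Precision matters in this trial. The sample is a convenience sample, the protocol's own power table runs from 0.39 to 0.78, and on event rates it states that "we do not have documented event rates from our targeted patient population". If one arm happens to receive more frequent admitters, nothing in the specified baseline data guarantees that this will be seen, and nothing in the fixed part of the model corrects for it. A baseline count would also give a first estimate of the admission rate in the target population, although it would not change a sample size set by feasibility.

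**Working it through.** **Which passages bear on the point.** Set side by side, the baseline list, the additional baseline variables, the strata, the a priori covariates and the examples for contingent adjustment all omit prior admissions. Three items leave room for them without requiring them: medical history, a separations file with no date window, and an open list of contingent covariates.

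**The plan's own figures.** The protocol gives no figure on this point. The completer number reproduces: 318 × 0.85 = 270.3, or 135 per arm if allocation is equal (assumed from the block sizes). The pilot usual-care rate is 32/30 = 1.07 per two years, and a 25% reduction gives 1.07 × 0.75 = 0.80. The power table reproduces only roughly: a pooled two-proportion test at 135 per arm, two-sided 0.05, gives 0.406, 0.511, 0.696 and 0.822 against the stated 0.39, 0.55, 0.67 and 0.78. Nothing below rests on that table.

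**Size of a chance imbalance.** The standard error of a standardised baseline difference is √(2/135) = 0.122. The 95% range is therefore ±1.96 × 0.122 = ±0.24 SD.

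**What such an imbalance does.** The shift in the outcome is roughly the imbalance times the prior/later correlation. For correlations of 0.19 to 0.40, this is 0.24 × 0.19 = 0.05 SD to 0.24 × 0.40 = 0.10 SD. Simulation of the unadjusted proportional-odds model (rates 1.07 v 0.80, gamma-distributed patient rates, 300 runs per scenario) found that an imbalance of 0.24 SD multiplied the odds ratio by about 1.08, 1.24 and 1.33 at frailty variances 0.5, 1 and 2. At variance 1, an average odds ratio of 0.73 would read about 0.73 × 1.24 = 0.90.

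**What adjustment gains.** All rows use 270 completers, a rate ratio of 0.75, two-sided alpha 0.05, and a proportional-odds model with and without log(1 + prior two-year admissions). Frailty variances and correlations are assumptions; the documents give none.

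| Usual-care rate | Patient-rate model | Prior/later correlation | Runs | Power without | Power with |
|---|---|---|---|---|---|
| 1.07 | log-normal, prior only partly shared | 0.19 | 1,500 | 0.36 | 0.37 |
| 1.07 | log-normal, prior only partly shared | 0.32 | 1,500 | 0.34 | 0.38 |
| 1.07 | log-normal, prior only partly shared | 0.40 | 1,500 | 0.28 | 0.32 |
| 1.07 | gamma, variance 1, fully shared | 0.46 | 350 | 0.32 | 0.40 |
| 0.70 | gamma, variance 1, fully shared | 0.38 | 300 | 0.23 | 0.29 |

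In the two gamma rows the mean z statistic moves from 1.480 to 1.665 and from 1.257 to 1.373. The equivalent gains in sample size are (1.665/1.480)² = 1.27 and (1.373/1.257)² = 1.19. Shorter runs over frailty variances 0.5 to 2 (150 runs each, Monte Carlo SE about 0.04) gave gains of about 0.01 to 0.12. A further set at 1.07 v 0.80 with correlations of 0.25 to 0.48 (400 runs each) gave about 0 to 0.09.

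The covariate in every row is a two-year prior count. A 12-month count was not simulated; it carries less information, so its gain would be expected to be smaller.

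**The case against.** **A reader might infer that prior admissions will never be measured, checked or adjusted for.** The documents do not support that. Medical history may capture some admissions, the baseline list is not exhaustive (depression appears only in a later paragraph), the separations request neither includes nor excludes a look-back, and the list of contingent covariates is open. What stands is narrower: prior admissions are not specified at any of these points. The contingent clause can work only if the variable has been collected.

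**A reader might infer that the primary result will be biased.** It will not. Allocation is randomised, and chance imbalance is already reflected in the type I error and the interval. The loss is in precision and in how credible one realised result looks.

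**The detail may belong in an analysis plan that is not shown.** That is fair for coding and form design. But the protocol itself fixes the a priori covariates and lists the baseline data, and a later plan cannot adjust for something nobody recorded or requested. Age and sex with an imbalance clause is a defensible choice, but adjusting only after seeing an imbalance is weaker than pre-specifying a prognostic covariate.

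**The gain is small and driven by assumptions.** This stands. A gain of 0.01 over 1,500 runs, where each power has a Monte Carlo SE of about √(0.36 × 0.64/1,500) = 0.012, is indistinguishable from none. Adjustment does not turn low power into adequate power.

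**Conclusion.** The point holds as a gap in specification. The protocol does not name admissions before randomisation as a baseline variable, states no look-back for a file it already requests, and pre-specifies no adjustment for the direct baseline counterpart of its primary outcome. The illustrative power gain is about 0 to 0.1. It rests on 135 completers per arm, a 25% reduction, overdispersed counts, a two-year prior count and an assumed prior/later correlation between about 0.2 and 0.5. The direction is well supported; the size is not known. Protection against a chance imbalance of up to about 0.24 SD is the second benefit. The low starting powers in the table come from modelling overdispersed counts and should not be read here as a finding against the protocol's power table. The change is worth making because it is cheap, not because the analysis is invalid without it.

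**What to change.** 1. **Baseline Assessment:** add the number of hospital admissions over one defined look-back, for example the 12 months before randomisation, to the existing chart abstraction and telephone confirmation.
2. **Study Outcomes and Healthcare Utilization:** state the same look-back for the hospital separations file, to confirm the abstracted count.
3. **Statistical Analyses:** add log(1 + prior admissions) to the a priori covariates beside age and sex.
4. **Interim analyses:** use the same look-back and the same source as in the final analysis. Do not replace a short abstracted count with a longer linked one part-way through.

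**Cost.** One form item, a longer period in an existing data request, possibly an added line in the consent form or ethics submission (the consent pages are not available to check), and one model term. The treatment odds ratio becomes conditional on prior admissions and will not equal the odds ratio without that covariate, so the report should say which one is primary.
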